#### Criteria for discontinuing or modifying allocated interventions {11b}

The following are the criteria for discontinuing allocated intervention:
SepsisNECWithdrawal of parental/guardian consentPoor feeding tolerance defined as increasing abdominal distension > 2 cm between inter-observer measurement and/or regurgitations after feeding > 3 feeds per day

#### Strategies to improve adherence to interventions {11c}

Medical notes (MN) of infants included in the study will be visibly marked to promote adherence to the study protocol. A flowchart explaining inclusion, exclusion, and discontinuation criteria will be available in the patient’s MN.

#### Relevant concomitant care permitted or prohibited during the trial {11d}

Participants should continue to receive standard neonatal care. Interventions aimed at improving weight gain such as increased daily intake (> 160–170 ml/kg/day) or increased dosing of vitamin D (> 1000 IU/l) or prescription of milk formula will be forbidden.

#### Provisions for post-trial care {30}

The standard of care provided in participating units is high. Participating in the clinical trial will not pose any direct benefit related to extra medical care or higher standard of care during hospitalization. Ancillary care (medical care provided to clinical trial participants during a trial, which is not related to the research question) will be thus very limited. For example, more frequent contact with the attending neonatologist and neonatal nurse may be perceived as beneficial by the parents (more occasions to ask questions, also those not related to the trial). Similarly, follow-up visits and the opportunity to meet an experienced psychologist may become an opportunity to discuss parental concerns not related to our research question. Apart from out-patient follow-up appointments (as per protocol), we do not plan any additional post-discharge care. In our experience, both these factors are perceived as benefits by the participating families and contribute to their decision to participate in research projects. However, during our introductory meeting with the parents of an eligible infant, we always emphasize that the decision not to participate will not influence standard of care provided to their child in any way.

### Outcomes {12}

#### Primary outcome

Weight gain velocity (grammes per week) will be measured daily starting from the day infants regain their birth weight up to 4 weeks, then weekly until discharge. Length and head circumference will be measured in centimetres weekly until discharge.

#### Secondary outcomes

Growth (weight, length, head circumference) will be assessed at discharge and at 4 months of corrected age.Body composition (percentage of body fat, fat mass, fat-free mass) will be measured at discharge and at 4 months corrected age by air plethysmography (PeaPod).^1^Neurodevelopmental outcome:
12 months corrected age: BSID-III (Bayley Scale of Development Third Edition); the following stratification of index composite scores will be used in our study:< 70 (> 2 SD below the mean)—severe impairment70–84 (> 1 SD below the mean)—mild impairment≥ 85—normal development3.5 years of corrected age: BSID and WPSSI-IV (Wechsler Preschool and Primary Scale of Intelligence, Fourth Edition IV).Behavioural problems: parental assessment by CBCL (Child Behaviour Check List) at 3.5 years corrected age.Feeding tolerance under whole period of fortification.Morbidity: incidence of necrotizing enterocolitis (NEC), retinopathy of prematurity (ROP) and bronchopulmonary dysplasia (BPD), intraventricular haemorrhage (IVH), periventricular leukomalacia (PVL), sepsis, and pneumonia. Definitions provided below.

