##### Secondary objectives

*Key secondary objectives*

The key secondary objectives are to determine the following anthropometric parameters in preterm infants born at ≤ 32 weeks of gestation at discharge and at 4 months:
Feeding toleranceVelocity of weight gainLength and head growthBody composition (by air displacement plethysmography, PeaPod)

*Other secondary objectives*
Neurodevelopmental outcome:
12 months corrected age: BSID-III (Bayley Scale of Development Third Edition)3.5 years of corrected age: BSID and WPSSI-IV (Wechsler Preschool and Primary Scale of Intelligence, Fourth Edition IV)Behavioural problems: parental assessment by CBCL (Child Behaviour Check List) at 3.5 years corrected ageTo compare the incidence of NEC, retinopathy of prematurity (ROP), and bronchopulmonary dysplasia (BPD) between both study groups

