**Table 2 Tab2:**
[figure not shown]
Enrolment, interventions, and assessments schedule

*DOL* day of life, *T1* enteral nutrition 80 ml/kg/day of own mother’s milk or human donor milk, *T2* 4 weeks of life, *T3* 8 weeks of life, *T4* 12 weeks of life/discharge, *T5* 4 months of corrected age, *CBC* complete blood count, *BUN* blood urea nitrogen

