### Statistical methods

#### Statistical methods for primary and secondary outcomes {20a}

Baseline characteristics will be presented for all included neonates in intention-to-treat and per-protocol analysis sets, by treatment group. Dichotomous variables will be presented as frequencies, categorical variables as median and interquartile ranges, and continuous variables as mean and standard deviations, along with 95% CI. In cases of missing data, i.e. due to adverse events or dropouts, in follow-up analysis, a weighted average taking account of changes in the gender ratio will be applied. Continuous variables will be tested against normality of distribution and the equality of variances between groups. For continuous variables distributed normally, the differences in means will be tested using *t* test; for continuous variables not distributed normally and for categorical variables between groups, comparison will be performed using the Mann-Whitney *U* test. The primary outcome will be assessed with one-tailed unpaired two-sample *t* test for noninferiority. Secondary and safety outcomes will be tested for two-sided superiority. Proportions of dichotomous variables will be tested using chi-square or Fisher’s exact test, whichever appropriate. In addition, the risk ratio (RR), the odds ratio (OR), and the number needed to treat will be assessed. For secondary outcomes, the difference will be considered significant when *p* value calculated in statistical tests will be < 0.05 or when the 95% CI for the mean difference will not include 0, or 1 in case of RR or OR.

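### In-hospital size and body composition are compared at discharge, with no fixed post-conceptional age or age standardisation stated; this costs precision and, if discharge depends on weight, shrinks a true difference in size

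*Protocol article*

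**What the plan says.** In the protocol article, Outcomes {12}, Secondary outcomes: "Growth (weight, length, head circumference) will be assessed at discharge and at 4 months of corrected age". The next item reads: "Body composition (percentage of body fat, fat mass, fat-free mass) will be measured at discharge and at 4 months corrected age". Secondary objectives lists these measures as key secondary, "at discharge and at 4 months". The footnote to Table 2 labels the in-hospital visit T4 as "12 weeks of life/discharge"; the table itself is not shown.

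Statistical methods {20a} gives the comparison: "For continuous variables distributed normally, the differences in means will be tested using *t* test", with the Mann-Whitney test for variables that are not normal. Neither this section nor the outcome sections mention z-scores, a fixed post-conceptional age for the discharge measures, or age at measurement as a covariate. The Inclusion criteria set an upper gestational-age limit of 32 weeks and no lower one. Sequence generation {16a} stratifies by delivery mode only.

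Elsewhere the trial does fix maturity. BPD is assessed at 36+0 weeks, the abstract ends its growth window at 36 weeks post-conceptional age or discharge, and follow-up visits use corrected age.

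**The concern.** There are two separate issues.

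**Precision.** Infants born at very different gestational ages are discharged at different maturity, and size depends strongly on maturity. An unadjusted comparison of size at discharge carries that spread as noise. The T4 label adds to it by joining postnatal age with discharge.

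**Possible attenuation.** Discharge comes after treatment starts, and treatment is meant to change weight gain. If the decision to discharge depends on weight, infants who grow faster tend to leave sooner and are measured younger. Part of a true difference in size then appears as earlier discharge instead of greater weight. How much depends on how discharge is decided, and the article does not say.

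At stake is whether a key secondary result of no difference in size at discharge could be read as no effect on growth.

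**Working it through.** The plan states no figure for size at discharge, so there is none to reproduce. The checks below illustrate what its choices imply.

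**1. Pure weight threshold (extreme case).**
- From Sample size {14}: weight gain of 19.3 g/kg/day (standard) and 21.2 g/kg/day (targeted).
- Assumed: exponential growth, start weight W0, discharge on reaching W1.
- Days to discharge: t = ln(W1/W0)/g.
- For 1200 to 2000 g, ln(2000/1200) = 0.5108. Standard: 0.5108/0.0193 = 26.5 days. Targeted: 0.5108/0.0212 = 24.1 days. The gap is 2.4 days.
- Difference at discharge: 2000 − 2000 = 0 g.
- Difference on day 26.5: 1200 × exp(0.0212 × 26.47) − 2000 = 2103 − 2000 = 103 g.
- Other assumed starts with the same threshold: 57 g from 1500 g and 141 g from 1000 g. Over starts of 900 to 1500 g and thresholds of 1800 to 2200 g, the range is 33 to 202 g.

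**2. Other discharge rules.** A simulation used 100 infants per arm and 3000 replicates. From the protocol: the two growth rates and the SD of 3.75 g/kg/day. Assumed: gestational age uniform from 25 to 32 weeks; growth starting 10 days after birth; median start weight rising log-linearly from 0.75 kg (25 weeks) to 1.7 kg (32 weeks), with log SD 0.15. The discharge rules were also assumed: a threshold of 2.0 kg (SD 0.15); the same threshold plus a minimum age (mean 36 weeks, SD 1); or age alone (mean 37 weeks, SD 1.5). Power is the chance of a significant two-sided t test favouring targeted fortification.

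| Discharge rule | Difference at discharge | Power, weight at discharge | Difference at 36 weeks | Power, weight at 36 weeks | Power, velocity |
|---|---|---|---|---|---|
| Weight threshold | 0 g | 2% | 226 g | 67% | 95% |
| Threshold plus minimum age | 214 g | 50% | 225 g | 66% | 94% |
| Age only | 324 g | 49% | 223 g | 65% | 95% |

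The effect vanishes only in the first row. In the other two a real difference remains, but weight at discharge has about 16 percentage points less power than weight at a common age.

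The 36-week columns assume every infant is weighed at 36 weeks, so they are a benchmark. Under the threshold rule many would have left before then. A 1.2 kg start corresponds in this model to birth at 25 + 7 × ln(1.2/0.75)/ln(1.7/0.75) = 29.0 weeks. On the standard-arm rate, discharge then falls at 29.0 + 10/7 + 26.5/7 = 34.2 weeks. For such infants the correction has to come from standardising to the exact day of measurement.

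**3. Postnatal age.** At 12 weeks of life an infant born at 32 weeks is 32 + 12 = 44 weeks post-conceptional age. One born at an assumed 24 weeks is 24 + 12 = 36. The span of 8 weeks (7 if the youngest is born at 25) is an upper bound, because infants discharged earlier may be measured earlier.

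**The case against.** A reader might go further and infer that the plan compares raw values at a time which treatment moves, so that a growth effect cancels by construction. The documents do not support that reading.

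- **Cancellation.** It needs discharge to be triggered by weight, and no criterion is given. The article's maturity markers (bottle feeding at about 34 weeks, intervention to 37 weeks or discharge) leave room for an age-driven decision, under which the difference persists.
- **Raw values.** The outcome section names the measures, not the scale of analysis. A t test works equally well on z-scores, and the full protocol or analysis plan may specify them.
- **12 weeks of life.** Treatment cannot move a fixed postnatal age; it only spreads maturity.
- **Maturity spread as bias.** Randomisation balances gestational age on average, so the loss is in precision.
- **Other outcomes.** Weight-gain velocity is a rate and keeps about 95% power under every rule tried. The 4-month assessment is at a fixed corrected age. Equal weight does not force equal fat mass, fat-free mass or percentage fat, so the cancellation argument does not carry over to body composition.

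All of this stands, and it limits the point to size and body composition at discharge. It does not remove the point. The article itself fixes a post-randomisation time without common maturity for key secondary measures, and the only tests it names are unadjusted. The precision loss also appears where discharge is not triggered by weight alone.

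**Conclusion.** The point holds in limited form. As stated, discharge is a weak time point for in-hospital size. The firmer cost is precision: about 50% power at discharge against about 66% at a common 36 weeks in the simulated cases with a maturity element in discharge. Attenuation is conditional. It reaches 0 g against about 103 g only under a pure weight threshold on the assumed 1200 to 2000 g path, and is smaller or absent under the other rules tried. Start weights, gestational-age distribution and discharge rules are all assumptions. No size is estimated for length, head circumference or body composition. The primary velocity comparison and the 4-month results are largely unaffected, so this is an inexpensive improvement to a set of key secondary outcomes and does not threaten the main conclusion.

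**What to change.** - Define in-hospital weight, length and head circumference at 36+0 weeks post-conceptional age, or at discharge if earlier, from the measurements already planned up to discharge.
- Analyse them as sex- and age-specific z-scores at the exact day of measurement, and name the growth reference in advance. Keep the discharge values as supportive.
- State which clock governs the T4 visit.
- For body composition, keep the discharge scan and record post-conceptional age at the scan. Adjust for that age only in a sensitivity analysis, because it is a post-randomisation variable that treatment may affect.
- Report age at discharge by arm, so that any shift in timing is visible.

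The cost is revised outcome wording and a z-score calculation; no new visit is needed. There are two small downsides. Results depend on the chosen reference, and 36+0 weeks falls before the possible end of intervention at 37 weeks, so the last week of exposure is seen only in the supportive discharge values.

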##### Definitions

Feeding tolerance: defined as haemorrhagic residuals or vomiting bile until pathological causes are ruled out (intestinal obstruction or ileus) [17]. Gastric residuals and abdominal girth will not be checked routinely. Isolated green or yellow residuals will be considered unimportant.NEC (necrotizing enterocolitis): stage II or III. Stage II requires clinical manifestations of distended abdomen and radiological verification (intramural and/or portal gas). Stage III requires findings like in stage II and more severe clinical symptoms (shock, need for respirator). In surgery verified cases, no radiological verification is needed [18].ROP (retinopathy of prematurity): stages I to V, diagnosed by an ophthalmologist according to international criteria [19].BPD (bronchopulmonary dysplasia): need for oxygen, continuous positive airway pressure (CPAP), or mechanical ventilation at 36 + 0 weeks gestational age [20].IVH (intraventricular haemorrhage) [21].PVL [21].Early- and late-onset sepsis defined as a positive blood or cerebral fluid culture at less or more than 72 h of age, respectively [22].

Feeding tolerance has been chosen as an efficacy and harm outcome in order to evaluate whether TEN may impact milk absorption in the intervention group. Exclusive breastfeeding decreases the risk of NEC; however, the impact of TEN on the risk of developing NEC has not yet been studied. Blood culture confirmed early-onset sepsis (EOS) is a known risk factor for delayed implementation of EN and can impact the risk of late-onset sepsis (LOS). Diagnosis of EOS and LOS can be associated with intermitted withdrawal of enteral nutrition, BPD, IVH, and PVL which are markers of neonatal morbidity; hence, we decided to include them in our analysis.

Time schedule of enrolment, interventions (including any run-ins and washouts), assessments, and visits for participants is presented in Table 2.

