#### Implementation {16c}

A member [a physician not involved in the patients care] of the research team will prescribe the allocated fortification on the patient’s drug chart. Milk fortification is routinely done twice a day (at 8 am and at 8 pm) for each following 12-h nursing shift (Fig. 1). For the purpose of the study, TF will be integrated in this schedule and performed by experienced registered nurses (RNs). The intervention will be performed by a RN blinded to treatment allocation. Patient’s data along with the result of the allocation will be sent to the statistical team. The randomization list will remain with the statistical team for the whole duration of the study.

All randomized infants who are prematurely discontinued from study will be considered *off study intervention/on study* and will follow the same schedule of events as those infants who continue study treatment. All of these infants will be followed through 36 months as scheduled. Once an infant is enrolled or randomized, the study site will make every reasonable effort to follow the infant for the entire study period. Participants may withdraw from the study for any reason at any time.

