#### Adverse event reporting and harms {22}

##### Harms

We will define an adverse event as any untoward medical occurrence in a subject without regard to the possibility of a causal relationship. Adverse events will be collected after the subject has provided consent and enrolled in the study. All adverse events occurring after entry into the study and until hospital discharge will be recorded. An adverse event that meets the criteria for a serious adverse event (SAE) between study enrolment and hospital discharge will be reported to the local Ethical Committee. A serious adverse event for this study is any untoward medical occurrence that is believed by the investigators to be causally related to study intervention and results in any of the following: life-threatening condition (that is, immediate risk of death), severe or permanent disability, and prolonged hospitalization. Serious adverse events occurring after a subject is discontinued from the study will *not* be reported unless the investigators feel that the event may have been caused by the study drug or a protocol procedure. The following AE will be reported: feeding intolerance defined as vomiting and emesis, abdominal distention, and gastric residuals within 7 days after the introduction of TEN. SAE will include necrotizing enterocolitis and gastrointestinal obstruction occurring after the introduction of TEN. Adverse events will be collected within the e-CRF and reported in trial publications.

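### Feeding (in)tolerance is defined in three ways that do not match, so an infant stopped for poor feeding tolerance can have no event in the feeding-tolerance outcome

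*Protocol article*

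**What the plan says.** The outcome is defined under Outcomes {12}, Definitions: "Feeding tolerance: defined as haemorrhagic residuals or vomiting bile until pathological causes are ruled out (intestinal obstruction or ileus"). The same paragraph adds: "Gastric residuals and abdominal girth will not be checked routinely". Its purpose is also given there: "Feeding tolerance has been chosen as an efficacy and harm outcome in order to evaluate whether TEN may impact milk absorption in the intervention group". Secondary objectives lists feeding tolerance among the key secondary objectives.

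Under Secondary outcomes the observation window is "Feeding tolerance under whole period of fortification". Intervention description {11a} runs the intervention to 37 weeks post-conception age or discharge.

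Criteria for discontinuing {11b} takes an infant off the allocated intervention for poor feeding tolerance. The signs there are abdominal distension rising by over 2 cm between measurements, regurgitation at more than three feeds daily, or both.

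Harms {22} names a reportable adverse event: "feeding intolerance defined as vomiting and emesis, abdominal distention, and gastric residuals within 7 days after the introduction of TEN".

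Implementation {16c} keeps discontinued infants on study; they "will follow the same schedule of events as those infants who continue study treatment". Section {20c} keeps everyone in the intention-to-treat analysis regardless of adherence.

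**The concern.** The signs that end treatment for poor feeding tolerance are not among the signs that make up the outcome. No section makes such a stop an outcome event. An infant can thus be judged too intolerant to continue, remain in the denominator, and contribute nothing to the numerator. The label adds confusion: the outcome is called tolerance, but the events it lists are signs of intolerance.

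This matters because the outcome serves both efficacy and harm. A difference in stops is also foreseeable. Targeted fortification adds modular nutrients on top of the standard fortifier, and the protocol phases it in over three days to help tolerance. If one arm has more stops for distension or regurgitation, the reported outcome may not show it.

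**Working it through.** **The three definitions side by side**

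| Section | Use | Signs | Window |
|---|---|---|---|
| {12} Definitions | Secondary outcome | Haemorrhagic residuals, bile vomiting | Period of fortification |
| {11b} | Stopping the allocated intervention | Distension > 2 cm, regurgitation at > 3 feeds/day | While on intervention |
| {22} Harms | Named adverse event | Vomiting/emesis, distension, gastric residuals | 7 days after introduction of TEN |

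Three things follow from the text alone.

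1. The first two rows share no sign. A stop under {11b} is an outcome event only if bile or blood also occurs.
2. The distension limb of {11b} needs a measurement, yet Definitions says abdominal girth is not checked routinely. The same sentence takes gastric residuals, one of the Harms signs, out of routine checking. These passages must be reconciled.
3. The window in Secondary outcomes may mean the planned period (to 37 weeks or discharge) or each infant's actual period on fortification. On the second reading, signs after a stop are not counted.

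The Harms definition does not close the gap. It covers 7 days, of which the first three are step-up days ({11a}), while the intervention runs to 37 weeks or discharge.

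**Illustration of size**

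The protocol states no rate for this outcome or for discontinuation, so there is no figure to reproduce. Every input here is an assumption.

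- p: proportion with bile or blood among infants not stopped, the same in both arms
- w: proportion stopped for distension or regurgitation (TF = targeted, SF = standard)
- o: share of stopped infants who also have a recorded bile or blood sign

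Recorded proportion = (1 - w)p + w·o. Proportion if stops are counted = (1 - w)p + w.

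With p = 5%, w = 15% (TF) and 5% (SF):

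- o = 0: recorded 0.85 × 0.05 = 4.25% versus 0.95 × 0.05 = 4.75%, difference -0.5 points
- o = 0.5: 4.25 + 7.5 = 11.75% versus 4.75 + 2.5 = 7.25%, difference +4.5 points
- o = 1: 19.25% versus 9.75%, difference +9.5 points
- stops counted: 19.25% versus 9.75%, difference +9.5 points

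In general the recorded difference is (w_TF - w_SF)(o - p), and the difference with stops counted is (w_TF - w_SF)(1 - p). In percentage points:

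| p | w TF / SF | Stops counted | o = 0 | o = 0.5 | o = 1 |
|---|---|---|---|---|---|
| 5% | 10% / 5% | +4.75 | -0.25 | +2.25 | +4.75 |
| 5% | 15% / 5% | +9.5 | -0.5 | +4.5 | +9.5 |
| 5% | 20% / 10% | +9.5 | -0.5 | +4.5 | +9.5 |
| 10% | 10% / 5% | +4.5 | -0.5 | +2.0 | +4.5 |
| 10% | 15% / 5% | +9.0 | -1.0 | +4.0 | +9.0 |
| 10% | 20% / 10% | +9.0 | -1.0 | +4.0 | +9.0 |

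The window is not modelled separately. If observation ends at the stop, only signs seen before it count, which can only lower o.

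**The case against.** A stopping rule and an outcome may legitimately use different signs. The Definitions paragraph looks deliberate: it cites a source and dismisses isolated green or yellow residuals. Harms {22} also commits to recording every adverse event from entry to discharge, so distension and regurgitation need not go unseen. How a stopped infant is scored on a secondary outcome may be set out in an analysis plan that is not shown, and the assessment schedule (Table 2) is not visible.

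Much of this stands. Different signs alone are not an error, silence on scoring is not the finding, and general adverse-event recording gives some protection. It is not, however, a defined comparison of intolerance between arms, and the one feeding-intolerance event that is defined covers only 7 days. Three stated definitions of nearly the same thing, one of them resting on a measurement described elsewhere as not routine, remain unreconciled.

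A reader might go further and infer that stopped infants cannot be counted, that observation closes when they stop, or that the least tolerant infants are scored as tolerant. The documents do not support this. A stopped infant with bile or blood is counted. The end of the window is one reading of an ambiguous phrase, and {16c} points the other way. Nothing ranks distension or regurgitation as worse than bile or blood, and no scoring rule for stopped infants is given.

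**Conclusion.** The point holds as a mismatch of definitions and an ambiguous window. An infant discontinued for poor feeding tolerance without bile or blood has no event in what the protocol calls an efficacy and harm outcome, so a between-arm difference in intolerance can be understated. The mismatch in signs holds on either reading of the window.

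The size cannot be determined. Over the assumed range, a difference of 4.5 to 9.5 points with stops counted is recorded as -0.25 to -1.0 points at zero overlap of signs, about half of it is lost at half overlap, and nothing is lost at full overlap. These figures assume more stops in the targeted arm and an equal background rate of bile or blood; neither comes from the protocol. A single risk ratio should not be read out of such an illustration, because the gap in stops is an input to it, not a result. No sample-size figure depends on this point.

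**What to change.** - Reconcile the definitions in {11b}, Outcomes {12} and Harms {22}, including the reliance on distension where girth is not routinely checked. Which clinical signs apply is for the investigators, and the stopping rule need not change for statistical reasons.
- Name the outcome feeding intolerance.
- State one window for both arms: from randomisation to 37 weeks post-conceptional age or discharge, whether or not the allocated fortification continues. Section {16c} already keeps these infants on the same schedule.
- Record discontinuations for poor feeding tolerance under {11b} and compare them by arm, either as a component of the outcome with components shown, or as a separate outcome beside the bile and blood signs.

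The cost is outcome wording plus a field in the e-CRF for the reason for stopping; the protocol does not say that this reason is already captured. A composite would mix events of differing severity, which is why components should be shown. Separate reporting avoids that problem.
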